### Trial design {8}

The Sleep-RA trial will be carried out as a randomised controlled trial with a two-group parallel design. Participants (*n* = 60) will be allocated 1:1 to either CBT-i as treatment (intervention group) or to usual care (control group). Outcome assessments will be conducted three times for each participant: at baseline, after treatment (week 7) and at follow-up (week 26), as presented in Fig. 1.

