#### Exclusion criteria

Patients will be excluded if they: have had glucocorticoid administered by intramuscular, intra-articular or intravenous methods within the preceding 4 weeks; are on a continuous current daily intake of oral glucocorticoids >5 mg/day; have had a change in oral glucocorticoid dose within the preceding 3 months; have had prior or current professional non-pharmacological treatment for insomnia; work at night during the intervention, are pregnant or nursing a baby; have a current alcohol or drug-use disorder, according to their medical journal; have patient-related circumstances (physical or mental) that impede their ability to give informed consent and adhere to the programme.

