### Participant timeline {13}

The trial period for each participant is approximately 6 months, and includes 6 weeks of CBT-i for participants in the intervention group and 20 weeks of subsequent outcome assessments for both groups. All participants will complete the same outcome assessments at baseline, after treatment (week 7) and at follow-up (week 26), as presented in Fig. 1 and Table 2.

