### Assignment of interventions: blinding

#### Who will be blinded {17a}

Outcome assessments are conducted by project nurses specialising in rheumatology, medical laboratory technologists or neurophysiology assistants, all of whom will be blinded to participant allocation.

Application of PSG equipment and instructions on how to use the actigraph and subsequent analysis of data will be conducted by neurophysiology assistants at the DCSM. Patient-reported outcome measures will be collected via questionnaires on tablets handed out by a project nurse. To assess the outcome of disease activity, a project nurse will examine the joints of participants to identify the number of swollen and tender joints related to DAS28. Blood samples will be taken and analysed by a medical laboratory technologist.

[name] will conduct the CBT-i intervention and is therefore not blinded to participant allocation.

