#### Procedure for unblinding if needed {17b}

The trial design is open-label with only the outcome assessors being blinded so unblinding will not occur.

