### Data collection and management

#### Plans for assessment and collection of outcomes {18a}

Data will be collected from PSG, actigraphy, physical examination, blood samples, a medical journal and questionnaires as presented in Table 2 and as follows.

The data collected from PSG cover SE, SOL, WASO, TST, sleep stages, number of awakenings, apnoea-hypopnoea index and leg movements. The data collected from actigraphy cover SE, SOL, WASO and TST for 7 continuous nights. From the medical journal we will collect data on duration of RA, anti-rheumatic drugs and glucocorticoids. Questionnaires will provide data on patient-reported SE, SOL, WASO, TST, insomnia, sleep quality, fatigue, impact of RA, depressive symptoms, pain, functional status, HRQoL, patient global assessment, physician global assessment, sociodemographic information, lifestyle, RA-related information, comorbidity, duration of insomnia, antidepressant drugs and hypnotic drugs. From the physical examination we will obtain data on swollen joints and tender joints counts (of 28 examined joints), and we will collect data on CRP from serum samples.

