#### Adverse event reporting and harms {22}

Participants will be monitored throughout the period of the intervention to detect any unintended events.

Should a PSG show signs of a sleep disorder requiring further examination or treatment the participant will be contacted by DCSM after the final assessment is completed.

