#### Frequency and plans for auditing trial conduct {23}

The project management group meet twice a year and conduct an audit of the trial.

When a participant has completed self-reported questionnaires on the tablet used in this trial, the project nurse ensures that data are complete and imported to the electronic case report form. When objective sleep measures of PSG and actigraphy are completed, all data are assessed for completeness by a neurophysiology assistant. If any data are missing or of low quality, the participant is invited to a new assessment.

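### Every sleep disorder found on PSG that needs work-up waits until after week 26, with no stated exception for serious findings

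*Protocol article*

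**What the plan says.** Adverse event reporting and harms {22} sets both a trigger and a time. When a PSG shows signs of a sleep disorder "requiring further examination or treatment the participant will be contacted by DCSM after the final assessment is completed". The trigger is the protocol's own judgement of clinical need. The timing is stated without qualification.

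The schedule is in two places. Trial design {8}: "Outcome assessments will be conducted three times for each participant: at baseline, after treatment (week 7) and at follow-up (week 26". Participant timeline {13}: "All participants will complete the same outcome assessments at baseline, after treatment (week 7) and at follow-up (week 26". PSG is thus recorded at all three visits, and the final one is week 26.

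Among the PSG variables, Plans for assessment and collection of outcomes {18a} lists "sleep stages, number of awakenings, apnoea-hypopnoea index and leg movements". The only sleep-related items in the Exclusion criteria are night work during the intervention and patients who "have had prior or current professional non-pharmacological treatment for insomnia"; no sleep disorder other than insomnia is named.

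On handling of the recordings, Frequency and plans for auditing trial conduct {23} says that when they are completed "all data are assessed for completeness by a neurophysiology assistant", with a repeat assessment offered if data are missing or poor. Who will be blinded {17a} lists among the outcome assessors "neurophysiology assistants, all of whom will be blinded to participant allocation".

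**The concern.** The rule postpones contact for findings that the protocol itself classes as needing action, and treats the least and most serious of them alike. The protocol foresees such findings: it has a sentence for them, it records the apnoea-hypopnoea index and leg movements, and it does not screen out other sleep disorders at entry. In the CBT-i arm, six weekly sessions that include sleep restriction (Intervention description {11a}) fall between a baseline recording and any contact about it.

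What is at stake is the care of individual participants. The planned sample size, alpha and analysis are not in question. The statistical interest lies in how far the rule can be relaxed without harming the comparison.

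**Working it through.** **1. Interval from recording to contact.** Inputs: assessments at weeks 0, 7 and 26; contact after the last one.

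- Baseline PSG: 26 − 0 = 26 weeks.
- Week-7 PSG: 26 − 7 = 19 weeks.
- Cross-check with Participant timeline {13}: 6 weeks of treatment + 20 further weeks = 26.
- A finding first recorded at week 26 has little delay.

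These are intervals from recording to contact. The avoidable part starts only when someone qualified has read the recording, and the document gives no reading time. The intervals are therefore upper bounds on the avoidable delay.

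**2. Does anything in the protocol prevent earlier contact?**

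- The neurophysiology assistants who apply PSG and analyse its data are blinded, so contact need not depend on arm.
- Recordings are checked on completion and participants can be called back during the trial. This is a check of quality and completeness, not a clinical reading, but it shows that a route back to the participant exists.
- Relevant concomitant care {11d} bars only other professional non-pharmacological treatment for insomnia. Treating a different disorder is not barred.
- Statistical methods {20a} follows the ITT principle, so a participant who starts such treatment stays in the assigned group.
- Explanation for the choice of comparators {6b} encourages controls to keep their usual sleep patterns until follow-up. Acting on a contact would depart from that advice.

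**3. What earlier contact could cost in power.** Sample size {14} uses a two-sample pooled t test, two-sided 0.05, difference 6 points, SD 7.5. The noncentral t distribution gives 86.1% with 30 per arm and 80.7% with 26 per arm, matching the protocol.

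Now assume that a fraction p starts treatment and that it raises SE by d points. Both values are assumptions; the documents give neither. In an arm with uptake, SD′ = √(7.5² + p(1−p)d²). With equal uptake the difference stays at 6. With uptake in controls only, the difference becomes 6 − p·d, with SD′ in controls and 7.5 in the CBT-i arm. The same p is used at n=60 and n=52.

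| p, d | SD′ | Equal uptake, n=60 / n=52 | Difference, controls only | Controls only, n=60 / n=52 |
|---|---|---|---|---|
| 1/30, 3 | 7.52 | 86.0% / 80.5% | 5.90 | 84.9% / 79.3% |
| 2/30, 5 | 7.60 | 85.2% / 79.7% | 5.67 | 81.5% / 75.6% |
| 3/30, 5 | 7.65 | 84.8% / 79.2% | 5.50 | 79.0% / 72.8% |
| 3/30, 10 | 8.08 | 80.8% / 74.7% | 5.00 | 68.6% / 62.1% |

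Unequal uptake is possible because participants know their allocation: the trial is "open-label with only the outcome assessors being blinded".

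Only contact after a baseline PSG can affect the week-7 primary outcome. Contact after a week-7 PSG can affect week-26 outcomes only. For those, 6/7.5 = 0.80 is the standardised difference in Sample size {14}, so the same model applies. With 3/30 of controls and a benefit of 5/7.5 = 0.67 SD, power at n=60 goes from 66.8% to 56.2% at the 0.01 threshold, and from 73.5% to 63.6% at 0.05/3.

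The table prices the remedy. It is not evidence of the problem.

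**4. Timing of an amendment.** From Trial status: 17 December 2018 to 16 January 2020 is 56.4 weeks; 17 December 2018 to 30 October 2020 is 97.6 weeks. This version therefore falls about 56 weeks into a period of about 98.

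**The case against.** The strongest reply is that this is a deliberate and open trade-off. The comparator is usual care with undisturbed sleep habits, the timing is stated plainly, and the trial has ethics approval. Contact in mid-trial adds sleep treatment that is not part of either arm, and with 52 participants there is almost no power to spare: one control in 30 with a 3-point benefit already gives 79.3%. This stands as a reason not to recommend prompt contact for every finding that meets the protocol's threshold. A reader might infer that recommendation from the rule's own wording, but on it reasonable statisticians can differ. The reply does not justify having no exception for the most serious findings.

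The second reply is that avoidable delay is not shown, because no clinical reading in mid-trial is described. This also stands, and it limits the claim. A reader might infer that staff know of a disorder, perhaps before randomisation, and withhold it for half a year. The documents do not support that, since the check they describe is for completeness and quality.

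The third reply is that an urgent-findings procedure may sit in the full protocol or the participant information, neither of which is shown. That weakens the point about a missing exception. It does not remove it, because this article states the timing itself, and an exception elsewhere would need this sentence to allow for it.

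Finally, a reader might see a contradiction with the statements that the intervention carries little or no risk and needs no data monitoring committee. There is none: those statements concern harm from the intervention, not disorders that PSG happens to reveal.

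**Conclusion.** The point holds as a limited patient-safety improvement. As written, contact about any PSG finding that the protocol says needs action comes about 26 weeks after a baseline recording and about 19 weeks after a week-7 recording, with no stated exception for serious findings. This rests only on the stated rule and schedule. The avoidable share of the delay and the number of participants concerned are unknown, because neither reading times nor prevalence are given.

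The general deferral can stay. A narrow exception is compatible with blinding, with the concomitant-care rule and with the ITT analysis. It should touch fewer participants than the full threshold would. How many is an assumption; if it were 1 in 30 per arm with a 3-point effect, power would go from 86.1% to 86.0% at n=60 and from 80.7% to 80.5% at n=52.

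**What to change.** In Adverse event reporting and harms {22}, keep contact after the final assessment for non-urgent findings and add an exception. DCSM, blinded to allocation, contacts a participant in either arm as soon as a PSG has been read and meets serious-finding criteria that DCSM has fixed in advance. Record any resulting treatment by arm, and keep the participant in the ITT analysis. State that acting on such contact is an exception to the advice given to controls under Explanation for the choice of comparators {6b}.

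Costs: a changed sentence, matching participant information, and ethics approval by the route in the section on protocol amendments {25}. If DCSM reads recordings in batches, which the document does not say, they would have to be read earlier. Because the change comes part-way through, earlier and later participants would be handled differently; report the amendment date and the numbers contacted before and after it. Some dilution is possible if a few participants start treatment, most of all if they are mainly controls and only 52 participants remain.

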#### Frequency and plans for auditing trial conduct {23}

The project management group meet twice a year and conduct an audit of the trial.

When a participant has completed self-reported questionnaires on the tablet used in this trial, the project nurse ensures that data are complete and imported to the electronic case report form. When objective sleep measures of PSG and actigraphy are completed, all data are assessed for completeness by a neurophysiology assistant. If any data are missing or of low quality, the participant is invited to a new assessment.

#### Plans for communicating important protocol amendments to relevant parties (e.g. trial participants, ethical committees) {25}

Important protocol amendments which may impact the content or conduct of the trial will be decided in the steering group. Important protocol amendments will be sent for approval to the ethics committee, notified to the participating sites and addressed in the written and oral information. Furthermore, the protocol registered on www.clinicaltrials.gov will be updated prior to implementation.

### Dissemination plans {31a}

We plan to publish two scientific papers in peer-reviewed journals based on the trial and to disseminate the results to patient organisations and the public through printed and electronic media.

## Discussion

The Sleep-RA trial is designed to investigate the efficacy of CBT-i on sleep and prevalent symptoms of fatigue, impact of RA, depressive symptoms, pain, functional status and HRQoL in patients with RA. To our knowledge, this is the first trial to investigate an evidence-based non-pharmacological intervention that, first and foremost, targets sleep-related cognitions and behavioural challenges related to sleep disturbances in this population.

Patients with RA have increased risk of fatigue, depressive symptoms, pain, reduced functional status and work capability. The severity of these symptoms is often linked to the disease activity, and patients with symptoms report that they feel constantly reminded of their chronic disease. The degree and duration of the above-mentioned symptoms is unpredictable because of the fluctuating character of RA. Living with one or more of these symptoms or the awareness that they can occur unexpectedly at any time can challenge the patient’s ability to manage the arthritis and their daily life. According to Spielman’s conceptual “3P model” of insomnia, insomnia is caused by precipitating events such as a change in health [100, 101]. Therefore, it is possible that there is an increased risk of initial insomnia around the time of diagnosis or when patients have arthritis flares and experience symptoms, while not knowing how long they will last. The development of chronic insomnia is complex, and is mainly—if not solely—mediated by perpetuating mechanisms [30]. RA symptoms are unpredictable, and because sleep disturbances are also associated with many of the same symptoms as RA, e.g. fatigue, depressive symptoms, pain and HRQoL, this could trigger, maintain and extend perpetuating mechanisms. In the persistent search for better sleep quality and more sleep, patients can develop a hyper-focus on their lack of sleep. This often increases the patient’s risk of obsession with sleep, followed by cognitions and behaviour that work against falling asleep [30, 36].

A positive effect of CBT-i will document CBT-i to be an applicable and pertinent treatment of insomnia in patients with RA, as recommended in international guidelines for non-pharmacological treatment of insomnia [62]. In addition, if the trial also finds positive effects regarding the secondary outcomes, such as fatigue, depressive symptoms, pain, disease activity and functional status, CBT-i will not only be relevant as a non-pharmacological treatment option for insomnia but will also have the potential to contribute positively in the management of symptoms related to RA and insomnia.

The primary outcome in Sleep-RA is SE which can be measured in different ways, e.g. with PSG, actigraphy, PSQI and a sleep diary. Although PSG is perceived as the most valid measure for SE [69], we are aware that PSG could inconvenience the participants in terms of the application of electrodes. Nevertheless, we found it necessary to ensure that a measuring method of high quality was used to generate results and because Sleep-RA is the first trial to examine CBT-i in patients with RA.

CBT-i is most often carried out by psychologists or other professionals with training in psychology in private clinics. Consequently, CBT-i is generally not accessible at hospitals, either as a part of the patient’s current treatment for RA or in the management of their symptoms. It is highly relevant to investigate the effect of nurse-led CBT-i in patients with RA since significant positive effects of CBT-i delivered in a group format by nurses have been shown in randomised controlled trials in European general practice settings [52, 53].

For future clinical purposes, we expect positive results from Sleep-RA to contribute to increased awareness of insomnia in rheumatology clinical practice. CBT-i has the potential to contribute significantly to the treatment of insomnia and, consequently, CBT-i has the potential to reduce the prevalence of chronic insomnia. Many symptoms of RA and insomnia are identical and some of them can be challenging to treat. CBT-i may also have comprehensive positive effects on the wide range of symptoms and thereby potentially contribute to increased physical and mental health and well-being in patients with RA.

## Trial status

This is protocol version 1, 16 January 2020.

Initial release was on 30 November 2018. Recruitment started on 17 December 2018, with an anticipated primary completion date of 30 October 2020.

## Data Availability

Any data required to support the protocol can be supplied on request.

## Abbreviations

BRAF-MDQ: Bristol Rheumatoid Arthritis Fatigue Multidimensional Questionnaire
BRAF-NRS: Bristol Rheumatoid Arthritis Fatigue Numerical Rating Scale
CBT-i: Cognitive behavioural therapy for insomnia
CRP: C-reactive protein
DANBIO: The National Clinical Database for Rheumatology
DAS28: Disease Activity Score-28
DCSM: Danish Center for Sleep Medicine
HADS-D: Hospital Anxiety and Depression Scale-Depression
HRQoL: Health-related quality of life
ICSD-3: International Classification of Sleep Disorders third edition
ITT: Intention-to-treat
MD-HAQ: Multidimensional Health Assessment Questionnaire
PSG: Polysomnography
PSQI: Pittsburgh Sleep Quality Index
RA: Rheumatoid arthritis
RAID: Rheumatoid Arthritis Impact of Disease
SE: Sleep efficiency
SF-36: Short Form-36 health survey
SOL: Sleep onset latency
TST: Total sleep time
VAS: Visual analogue scale
WASO: Wake after sleep onset
